### Exclusion criteria

The exclusion criteria were as follows: (a) any inflammatory arthritis (e.g. gout, reactive arthritis, rheumatoid arthritis, psoriasis, psoriatic arthritis, seronegative spondyloarthropathy) or systemic lupus erythematosus; (b) previous or planned knee replacement or surgery including arthroscopy within 12 months; (c) severe valgus knee deformity (angle of genu valgum > 30°); (d) contraindication to MRI; (e) use of intra-articular, intra-muscular, or oral corticosteroids in previous 4 weeks; (f) use of other anti-synovitis agents (e.g. hydroxychloroquine or sulphasalazine) in previous 3 months; (g) any clinically significant condition(s) such as (but not limited to) active cancer including lymphoma, and renal (e.g. abnormal renal function), hepatic (including active hepatitis B, hepatitis C, abnormal liver function), severe respiratory (e.g. lung infection, pulmonary fibrosis), haematological (e.g. white cell count < 4 × 10^9^/L, platelets < 100 × 10^9^/L, or haemoglobin < 100 g/L), gastrointestinal, endocrine, cardiac, neurologic, or cerebral diseases; (h) history of infections such as syphilis and HIV; (i) highly allergic to MTX; and (j) pregnant or lactating women.

### Randomisation/blinding

Allocation of participants will be based on computer-generated random numbers using block randomisation. To control for variation in centres, the randomisation will be stratified according to the centres. The RCT will be blinded to participants, investigators, and those measuring the effect of the intervention. Allocation concealment will be ensured by the use of a central automated allocation procedure, with security in place to ensure allocation data cannot be accessed or influenced by any person. Participants will be assigned to the interventions after baseline screening. Sequentially numbered and sealed opaque envelopes which reveal random numbers will be provided to the centres. Identical drugs for each participant will be allocated by research nurse base on the corresponding random number. Objective measures of knee structural changes and knee pain will be made by trained observers who are blinded to group allocation. The statistician who performs the statistical analyses will also be blinded. Unblinding will be allowed in emergency that affects the safety of participants. We will withdraw the unblinded participants but will continue to follow-up as per planned schedule.

### Intervention

After randomisation, participants in the intervention group will receive MTX (start from 5 mg per week for the first 2 weeks and increase to 10 mg per week for the second 2 weeks and 15 mg per week for the remaining period if tolerated). Plasma levels of oral MTX in a dose of 15 mg per week were similar as in a dose of 20 mg or 25 mg per week [19], so a maximal dose of 15 mg per week will be used in this study. The dose can be modified at the rheumatologist’s discretion regarding its intolerance or laboratory abnormalities [e.g. medication will be ceased if aspartate or alanine aminotransferase (AST, ALT) level greater than 3 times the upper limit of normal, or if AST or ALT level greater than twice the upper limit of normal on 2 continuous occasions; the dose will be reduced until 5 mg if AST or ALT level is raised but does not reach the level mentioned above]. The control group will receive an identical inert placebo per week. To reduce possible side effects, weekly doses of folic acid 5 mg will be given 1 day after MTX usage. This dose of folic acid is safe and may have additional benefits such as cardiovascular reduction [20]. Because skin dryness, skin rashes, and increased risk of skin malignancy (esp melanoma) may occur, the participants will be advised to wear a hat when out in the sun. Alcohol is avoided while on this medication. “Patient information on MTX” from the Chinese Rheumatology Association will be provided to all participants.

During the trial, all participants will not be asked to stop their analgesic medications, so specific medication will be recorded including the dosage and duration. However, corticosteroids may significantly affect the evaluation of outcomes, so their use will not be allowed. Trimethoprim (*Bactrim or Septra*), an antibiotic often used for respiratory and urinary infections, may increase the toxicity of MTX, so will also be disallowed in the trial. Participants who do not benefit from current study post-trial will be referred to appropriated outpatient treatments.

### Quality assurance

All research staff will be trained using the standard protocol ahead of the recruitment. The trial will be delivered in accordance with the protocol, and case report forms will be provided to the site staff. The investigators, research assistants, and outcome assessors are different people. Protocols will not be altered during the study timeframe.

### Outcome measures

The primary endpoints of the study will be effusion-synovitis volume and VAS pain. The secondary endpoints of the study will be IPFP signal intensity alteration measures, WOMAC total score and subscales, and OMERACT-OARSI responders.

#### Assessment of MRI structural changes

Knees will be imaged in the sagittal plane on a 3.0-T whole-body magnetic resonance unit with use of a commercial transmit-receive extremity coil. T2-weighted fast spin-echo and fat-saturated T1-weighted spoiled gradient echo sequences will be used. Changes in effusion-synovitis and IPFP signal intensity measures from baseline to week 52 are the endpoints, but we will also assess changes in total scores of cartilage defects and BMLs.
*Knee joint effusion-synovitis:* Knee effusion-synovitis maximal volume/area [13] at suprapatellar pouch will be measured at screening and week 52, and severity will be scored from 0 to 3 according to the estimated maximal distension of the synovial cavity by assessing the amount of intra-articular fluid-equivalent signal on T2-weighted MRI [21]. Effusion-synovitis at central portion, posterior femoral recess, and subpopliteal recess will also be assessed.*IPFP signal intensity alterations:* Signal intensity alterations within IPFP were defined as discrete areas of increased signal. Standard deviation of IPFP signal intensity[sDev(IPFP)] and Clustering Factor(H) will be used to represent the signal intensity alteration within IPFP. The measurements will be performed using sagittal planes of fat-saturated T2-weighted images [22] at screening and week 52.

#### Assessment of knee symptoms

Knee pain will be assessed by VAS (0–100) and Western Ontario and McMaster Universities Osteoarthritis Index (WOMAC) [23] at each time point. Knee function and stiffness will also be assessed using WOMAC. The WOMAC consists of 24 items covering three subscales: pain (5 items), stiffness (2 items), and physical function (17 items). Each subscale will be transformed to a score ranging from 0 to 10, with a higher score indicating greater pain and physical function impairment.

#### Other measures

*Cartilage defects:* The cartilage defects will be graded at screening and week 52 on T2-weighted MR images using a modified Outerbridge classification at medial tibial and femoral, lateral tibial and femoral, and patellar sites from grade 0 to 4. Intra-observer reliability (expressed as ICC) was 0.89–0.94, and inter-observer reliability from previous studies was 0.85–0.93 [18].*Subchondral BMLs:* The subchondral BMLs will be assessed at screening and week 52 on T2-weighted MR images and defined as discrete areas of increased signal adjacent to the subcortical bone at the lateral, medial femur and/or tibia. Based on the modified Whole-Organ Magnetic Resonance Imaging Score (WORMS) method [24], each BML will be scored on the basis of lesion size from grade 0 to 3 (if present on > 3 consecutive slices). The intraclass correlation coefficients (ICCs) in different sites from a previous study were 0.89–1.00 [25]. We have also developed BML maximum area as a sensitive measure of progression [26].*Radiographic OA:* This will be assessed at screening by a standing semiflexed anteroposterior radiograph of the diseased knee. Radiographic OA status will be assessed using Kellgren-Lawrence (grade 0–4). X-rays will also be scored for osteophytes and joint space narrowing on a 4-point scale (0–3) by two simultaneous observers utilising the OARSI atlas. This method has excellent reproducibilities with an ICC of 0.99 for osteophytes and 0.98 for joint space narrowing [27].*Angle of genu valgum:* This will be measured from weight-bearing radiographs at screening. Our intra-observer correlation coefficient was 0.98 [28].*General characteristics:* Age and sex will be recorded at each time point except screening. Height (stadiometer), weight (electric scales), and waist and hip circumference will be measured using standard procedures.*Quality of life:* The Short Form 12 (SF-12) item questionnaire which includes measures of physical function, general health, mental health, role-physical and role-motional, social functioning, vitality, and bodily pain level will be used to assess quality of life [29] at each time point except screening.*Depression*: The Patient Health Questionnaire-9 (PHQ-9) will be used at each time point except screening to measure and monitor the depression of participants [30].*Cigarette smoking status, previous knee injury, and occupation* will be assessed by questionnaires at baseline and week 52 [31].*Concomitant medication usages* such as glucosamine, chondroitin, and non-steroid anti-inflammatory drugs will be recorded by questionnaire at each study visit.

### Safety assessments

The safety profile of MTX has been studied for over 25 years, it is well tolerated by most patients in the weekly low doses used for RA treatment, and it is a well-known drug with a well-established side effect profile. Most patients do not experience side effects, and for those who do, many of the minor side effects will improve with time (American College of Rheumatology Guideline for MTX). Adverse events of MTX will be closely monitored at each visit during the study. The most common side effects include nausea, malaise, vomiting, diarrhoea, and stomach pain; mouth ulcers; skin dryness, skin rashes, and increased sensitivity to the sun; mild tiredness, headache, and mental clouding; and temporary increase in muscle and joint pain. Less common or rare possible side effects include infection, cytopenia, abnormal liver function with fibrosis, and non-infectious pneumonitis (presenting with dry cough, shortness of breath, ± fever). Should any serious adverse events (SAEs) occur, they will be recorded on a separate form and principal investigators (PIs) will be notified within 24 h. An independent safety monitoring board will be convened, consisting of two clinical rheumatologists, a clinical pharmacologist experienced in MTX use, and a biostatistician, all with clinical trial experiences. They will meet bimonthly or more often if SAEs occur, and provide a written report to the PIs. The dose of MTX will be modified based on the tolerance at the rheumatologist’s discretion.

### Sample size

The sample size calculations were performed based on formulae provided by Cohen [32] and based on the following parameters: (1) *α* = 0.05, 2-sided; (2) *β* = 0.20, power = 80%; and (3) our previous study reported that suprapatellar pouch effusion maximum area in older people with knee pain was 2.0 ± 1.5 cm^2^. To determine an expected rate of effusion-synovitis decrease after MTX treatment of 35% [33], the calculated sample size will be 74 per arm (Table 2). A study from our group reported that patients with knee OA had a VAS knee pain score (0–100) of 50 ± 20 [26]. Assuming knee pain in OA patients will be reduced by 20% following MTX treatment, the sample size needed to detect these differences is 64 per group (Table 2). A decrease in knee pain of 20% or more is deemed clinically relevant [34]. Therefore, 100 patients in each arm (allowing for a 20% dropout over 52 weeks) will be sufficient to detect the differences between the treatment and placebo groups. The participants will be recruited from 9 study sites, and competitive recruitment strategy will be implemented.

**Table 2 Tab2:** Sample size calculation

	Mean (SD)	Detectable difference	Calculated sample size (per arm)
Suprapatellar pouch effusion (cm^2^)	2.0 ± 1.5	35%	74
VAS knee pain (0–100)	50 ± 20	20%	64

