### Statistical analysis plan

Intention-to-treat and per-protocol (for patients who have taken > 80% the study medication) analyses of primary and secondary outcomes will be performed. The changes in outcome measures among all randomised participants at 52 weeks will be used for intention-to-treat analyses. Independent *t* tests and chi-square tests will be used to examine baseline characteristics of participants between groups. General linear mixed models to account for the effects of clustering by trial sites will be used to compare changes in outcomes in univariable and multivariable modelling between groups. Additional adjustment for imbalanced baseline factors will be made for further analyses. Baseline data will be used for data imputation assuming missing at random. A 95% confidence interval not including the null point or a *p*-value < 0.05 (two-tailed) will be considered statistically significant.

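### The sample size uses single-time SDs, but the planned comparison is of 52-week changes, so the stated 80% power is not established and could be too high or too low

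*Protocol article*

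**What the plan says.** The Sample size section fixes a two-sided α of 0.05 and 80% power. For the structural endpoint it states that "our previous study reported that suprapatellar pouch effusion maximum area in older people with knee pain was 2.0 ± 1.5 cm"², takes an "expected rate of effusion-synovitis decrease after MTX treatment of 35"%, and concludes that "the calculated sample size will be 74 per arm". For pain it reports that "patients with knee OA had a VAS knee pain score (0–100) of 50 ± 20", adds "Assuming knee pain in OA patients will be reduced by 20% following MTX treatment", and arrives at 64 per group. Table 2 repeats these inputs. Enrolment is then set at 100 per arm to allow for 20% dropout.

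The compared quantity is defined elsewhere. Under Assessment of MRI structural changes: "Changes in effusion-synovitis and IPFP signal intensity measures from baseline to week 52 are the endpoints". Under Statistical analysis plan: "The changes in outcome measures among all randomised participants at 52 weeks will be used for intention-to-treat analyses". That section compares changes between groups with mixed models that account for site, in univariable and multivariable form, and leaves adjustment for imbalanced baseline factors to further analyses. It does not name the baseline value of the outcome as a covariate. The article gives no SD of change and no baseline-to-follow-up correlation.

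**The concern.** The SD in a power calculation must be that of the quantity tested. Here 1.5 cm² and 20 points describe how people differ from one another at one time, whereas the planned comparison depends on how much their changes over a year differ. The two SDs coincide only for one particular correlation, which the article does not state.

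At stake is how the result will be read. The section concludes that 100 per arm is enough to detect the assumed differences. If the 52-week correlation is low, a null result on effusion-synovitis would be taken as stronger evidence of no effect than it is. If the correlation is high, the trial is better powered than the article says.

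**Working it through.** **Inputs from the Sample size section and Table 2.** α = 0.05 two-sided; power 80%; effusion mean 2.0, SD 1.5 cm², difference 35%; VAS mean 50, SD 20, difference 20%; 100 per arm with 20% dropout.

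**Step 1. Reproduce the printed figures** (two-sample t-test, noncentral t).
- Effusion: difference 0.35 × 2.0 = 0.70 cm²; 0.70/1.5 = 0.467; n = 73.05, rounded up to **74**.
- VAS: difference 0.20 × 50 = 10 points; 10/20 = 0.50; n = 63.77, rounded up to **64**.

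Both match, so the single-time SDs were used as the SD of the compared quantity. The dropout allowance is adequate: 74/0.8 = 92.5 and 64/0.8 = 80, both within 100. Expected completers are 100 × 0.8 = 80 per arm, where the single-time SDs give 83.5% power (effusion) and 88.2% (VAS).

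**Step 2. Put the SD on the change scale.** With equal variances at both times, SD_change = SD × √(2(1−ρ)). At ρ = 0.5 the factor is 1. At ρ = 0.3 it is √1.4 = 1.183, giving 1.775 cm² and 23.7 points. At ρ = 0.7 it is √0.6 = 0.775, giving 1.162 cm² and 15.5 points.

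**Step 3. Power of the unadjusted change comparison at 80 per arm.** ρ is an assumption, and the protocol's own differences are kept.

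| ρ | Effusion (0.70 cm²) | VAS (10 points) |
|---|---|---|
| 0.2 | 64.0% | 70.0% |
| 0.3 | 69.8% | 75.7% |
| 0.4 | 76.4% | 81.8% |
| 0.5 | 83.5% | 88.2% |
| 0.6 | 90.7% | 94.0% |
| 0.7 | 96.6% | 98.2% |

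Power reaches 80% at ρ of about 0.45 (effusion) and 0.37 (VAS). In evaluable patients per arm for 80% power, ρ = 0.3 needs 102 (effusion) and 89 (VAS); ρ = 0.7 needs 45 and 39.

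**Step 4. Effect of the VAS entry rule.** The Inclusion criteria require a VAS of at least 40 mm. If the baseline is a normal with mean 50 and SD 20 cut off below 40 (an assumption), its mean becomes 60.2 and its SD 13.9. Week 52 then has variance 400(1−ρ²) + ρ² × 13.9², and the change has variance (1−ρ)² × 13.9² + 400(1−ρ²). At ρ = 0.3 this gives SD_change = 21.4 and 83% power for 10 points at 80 per arm; at ρ = 0.2 it gives 22.5 and 80%. If the 20% reduction is applied to the higher mean (0.20 × 60.2 = 12.0 points), power is 94% and 92%.

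**Step 5. If the model adjusts for the baseline value.** The relevant SD is SD × √(1−ρ²), which never exceeds SD. At ρ = 0 and 80 per arm, power is 83.5% and 88.2%; at ρ = 0.3 it is 86.8% and 90.9%.

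**The case against.** The strongest reply is that nothing was miscalculated: 74 and 64 are correct for the inputs shown, and those inputs suit a change score when ρ = 0.5. That stands as far as it goes. But the article prints the inputs, the result and the conclusion that the numbers suffice, and those inputs support the conclusion only through a value of ρ that is not given.

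A second reply is that the multivariable model may include the baseline outcome, in which case the single-time SD is an upper bound. This limits the point without removing it. The article commits to unadjusted models and to multivariable models with unnamed covariates.

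A third is that the low end of the range is too pessimistic, and this partly stands. The VAS entry rule removes most of the pain shortfall. Effusion-synovitis grade ≥ 2 is also an entry condition, so the 2.0 ± 1.5 distribution will be altered by selection too, in a way the article does not allow one to quantify. If the treated arm's week-52 SD shrank in line with its 35% lower mean (an assumption), effusion power at 80 per arm would be about 76% at ρ = 0.3 and 82% at ρ = 0.4. The article also seeks a final MRI from participants who withdraw after about 24 weeks. With 90 evaluable per arm, effusion power would be 75% at ρ = 0.3 and 81% at ρ = 0.4.

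A reader might infer that the trial is underpowered, at about 70%. The documents do not support that. The figure needs ρ of about 0.3 for effusion or 0.2 for VAS, neither of which has a source in the article, and for ρ above 0.5 the single-time SD is conservative.

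**Conclusion.** The mismatch holds: the stated 80% power belongs to a comparison of single-time values, and for the unadjusted comparison of 52-week changes it is not established in either direction. Across ρ from 0.2 to 0.7, the uncertainty at 80 completers per arm spans about 33 percentage points for effusion (64% to 97%) and 28 for VAS (70% to 98%). A shortfall below 80% arises only at the lower correlations, and effusion has the higher threshold.

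These figures assume equal variances at both times, 80 evaluable per arm and the protocol's own differences. They ignore site clustering and the planned imputation from baseline data. Severity is minor to moderate: the justification needs repair, but the design does not.

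**What to change.** In the Sample size section and Table 2, replace the single-time SDs with the SD of the 52-week change, from longitudinal data if the group holds them. Otherwise state the assumed ρ and use SD × √(2(1−ρ)). Restate the power at 80 completers per arm over ρ of 0.2 to 0.7, leaving N unchanged.

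Alternatively, state in the Statistical analysis plan section that the primary model adjusts for the baseline value of each primary outcome. Given similar variances at both times, the single-time SD is then an upper bound, and power at 80 per arm is at least about 83% (effusion) and 88% (VAS).

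Either route costs some rewording and at most one recalculation, with no extra patients or procedures. On the first route, the stated power for effusion-synovitis may become less favourable.

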### Statistical analysis plan

Intention-to-treat and per-protocol (for patients who have taken > 80% the study medication) analyses of primary and secondary outcomes will be performed. The changes in outcome measures among all randomised participants at 52 weeks will be used for intention-to-treat analyses. Independent *t* tests and chi-square tests will be used to examine baseline characteristics of participants between groups. General linear mixed models to account for the effects of clustering by trial sites will be used to compare changes in outcomes in univariable and multivariable modelling between groups. Additional adjustment for imbalanced baseline factors will be made for further analyses. Baseline data will be used for data imputation assuming missing at random. A 95% confidence interval not including the null point or a *p*-value < 0.05 (two-tailed) will be considered statistically significant.

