If the primary hypothesis of this RCT is proven, MTX has the potential to be used for slowing disease progression and reducing knee pain for inflammatory OA. It would significantly delay the time to knee joint replacement which would be of major public health importance. This suggests great potential for substantial cost savings through reductions in joint replacement surgery as well as the potential for great improvements in quality of life for those with OA. The proposed study will also determine the safety and acceptability of MTX with the potential of being a cost-effective and innovative approach to the management of knee OA.

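### Two primary endpoints, each tested at two-sided 0.05 with no rule on whether one or both must succeed: if either suffices, the family-wise error is about 8–10%, not 5%

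*Protocol article*

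**What the plan says.** The Outcome measures section reads: "The primary endpoints of the study will be effusion-synovitis volume and VAS pain". The heading above the two hypotheses is plural, and the primary aim joins the two outcomes with the word *and*. The Discussion, by contrast, opens its closing argument with "If the primary hypothesis of this RCT is proven", in the singular.

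The Sample size section and Table 2 treat the endpoints one at a time. Each calculation uses two-sided alpha 0.05 and 80% power, giving 74 per arm for effusion and 64 per arm for pain. The section then sets 100 per arm, with a 20% dropout allowance.

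The Statistical analysis plan section says: "Intention-to-treat and per-protocol (for patients who have taken > 80% the study medication) analyses of primary and secondary outcomes will be performed". Mixed models "will be used to compare changes in outcomes in univariable and multivariable modelling between groups". Significance is defined once, for all outcomes: "A 95% confidence interval not including the null point", or a two-tailed p-value below 0.05. Adjustment for imbalanced baseline factors is described as additional and for further analyses.

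**The concern.** With two primary endpoints, the error rate of the trial's conclusion depends on the success rule. A trial that wins if either endpoint is significant, each at 0.05, has a false-positive rate above 5%. A trial that must win on both has an error rate of at most 5%, but its power is the joint power, which is lower than either single power. The protocol fixes the 0.05 for each endpoint without fixing the rule, so the reader cannot tell which case applies.

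This is more than detail left to a separate analysis plan. The sample size already spends the full 0.05 on each endpoint, and the significance sentence allows no exception. A later alpha split would depart from the basis on which the trial was sized.

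Discordant results are a realistic prospect. The Introduction reports that an earlier randomised methotrexate trial in knee OA modestly reduced pain on a numeric rating scale but had no effect on MRI synovitis. If that pattern recurred here, the protocol would not say whether the trial had succeeded, and the choice would be made with the results in view.

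**Working it through.** **Inputs from the Sample size section and Table 2.** Effusion: "suprapatellar pouch effusion maximum area in older people with knee pain was 2.0 ± 1.5 cm^2", with a 35% reduction, so the difference is 0.35 × 2.0 = 0.70 cm² and d = 0.70/1.5 = 0.467. Pain: 50 ± 20 with a 20% reduction, so the difference is 10 points and d = 10/20 = 0.50. Alpha is two-sided 0.05 and power 80%. There are 100 per arm with 20% dropout, so 80 completers per arm.

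**Assumptions not in the protocol.** The correlation ρ between the two endpoints' test statistics (range 0 to 0.8), and the correlation r between baseline and week 52 (0.3 or 0.5).

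**1. The plan's own figures.** n per arm = 2(1.960 + 0.842)²/d². Effusion: 15.70/0.2178 = 72.1, so 73; the t-test calculation gives 73.05, so 74. Pain: 15.70/0.25 = 62.8, so 63; the t-test gives 63.77, so 64. Both Table 2 figures reproduce, as single-endpoint calculations at 0.05. Dropout: 74/0.8 = 92.5, so 93, and the planned 100 exceeds this.

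**2. Power per endpoint at 80 per arm.** Noncentrality = d√(n/2), with √40 = 6.325.
- Effusion: 0.467 × 6.325 = 2.951; Φ(2.951 − 1.960) = 83.9% (t-test 83.5%).
- Pain: 0.50 × 6.325 = 3.162; Φ(3.162 − 1.960) = 88.5% (t-test 88.2%).

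**3. Error and joint power under each possible rule.** For uncorrelated endpoints, the either-endpoint error is 1 − 0.95² = 9.75%, and joint power is 0.839 × 0.885 = 74.3%. The other values come from the bivariate normal distribution.

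| ρ | Error if either suffices | Joint power if both required (unadjusted) |
|---|---|---|
| 0 | 9.75% | 74.3% |
| 0.3 | 9.5% | 76.0% |
| 0.5 | 9.1% | 77.4% |
| 0.8 | 7.8% | 80.4% |

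With t-test rather than normal powers, the value at ρ = 0 is 0.835 × 0.882 = 73.6%.

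**4. Power under Hochberg.** An endpoint is rejected if its own p < 0.025, or if both p < 0.05. Powers at 0.025 are 75.4% (effusion) and 81.5% (pain). At ρ = 0:
- Effusion: 0.754 + (0.835 − 0.754) × 0.882 = 82.5%.
- Pain: 0.815 + (0.882 − 0.815) × 0.835 = 87.1%.

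At ρ = 0.5, simulation gives 82.0% and 86.1%.

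**5. Effect of baseline adjustment.** The residual SD is multiplied by √(1 − r²): 0.954 at r = 0.3 and 0.866 at r = 0.5. At r = 0.5, d becomes 0.539 and 0.577, and power at 0.05 becomes 92.3% and 95.2%. Joint power at 80 per arm, for ρ from 0 to 0.5, is about 79–81% at r = 0.3 and about 88–89% at r = 0.5.

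**The case against.** The strongest reply is that the primary aim says *and*. If both endpoints are required, the error rate is at most 5%. The p < 0.05 sentence defines statistical significance, not trial success, and the singular in the Discussion is loose prose. All of this is fair. But an *and* in an aim is not a decision rule, so the 8–10% is conditional: it is the error rate under one permitted reading, not a property the protocol states.

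Three stronger readings might be inferred, and the documents do not support them.

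- **That the stated 80% power is false.** The Sample size section makes no joint claim. It gives two separate calculations, and both are met at 80 completers per arm. Joint power computed by pairing 74 and 64 per arm (about 65–69%) describes no planned trial, since 100 per arm are randomised for both endpoints.
- **That the error rate is near 20%.** Counting two endpoints, two analysis sets and two models as eight routes to success, null simulations gave roughly 17–20%. Those figures rest on an assumed random 80% per-protocol set and an assumed covariate structure, neither of which is in the protocol. Treating the eight tests as independent (34%) would overstate the error further, because they are highly correlated.
- **That failing to rank set and model is itself an error.** Naming the deciding set and model is commonly left to the analysis plan, which is not shown, and the wording on imbalance adjustment already suggests a secondary role. It is worth settling in the same edit, but it does not carry the point.

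**Conclusion.** The point stands in limited form. The protocol spends the full two-sided 0.05 on each of two primary endpoints and gives no rule for combining them. If success on either is enough, the family-wise error is about 8–10% over endpoint correlations from 0.8 down to 0. If both are needed, error is controlled and unadjusted joint power is about 74–77% for correlations 0 to 0.5, a shortfall of 3–6 points against 80% that disappears near 0.8 or with a reasonably predictive baseline. Per-endpoint power is as stated or better.

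The error figures depend only on the two tests at 0.05 and the assumed correlation. The power figures also take the planning means, SDs and dropout at face value, and treat the Table 2 SD as the SD of the quantity compared. For a simple change score, that is exact when baseline and week 52 correlate at 0.5, since √(2(1 − 0.5)) = 1.

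**What to change.** State the success rule in the protocol and analysis plan before unblinding.

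1. Name one primary analysis per endpoint: the ITT comparison at week 52, adjusted for site and for the baseline value of that outcome.
2. Test the two endpoints with Hochberg or Holm at family-wise two-sided 0.05, so that a claim on either one is valid.
3. Label the per-protocol analyses and further-adjusted models as supportive and unable to establish success.

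The cost is wording and a small loss of power, with no extra participants. At 80 completers per arm without baseline adjustment, Hochberg gives about 82–83% for effusion and 86–87% for pain, against 83.5% and 88.2% with no correction. Baseline adjustment raises these. At an assumed r = 0.5 and uncorrelated endpoints, powers at 0.025 are 87.3% and 91.6%, so Hochberg gives 0.873 + (0.923 − 0.873) × 0.952 = 92% and 0.916 + (0.952 − 0.916) × 0.923 = 95%.

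If the sponsor wants both endpoints to be required, say so, test each at 0.05, and report joint power for the analysis actually used: about 74–77% unadjusted, about 79–81% with an assumed baseline correlation of 0.3, and about 88–89% with 0.5. The unadjusted figure should not be attached to a baseline-adjusted primary analysis.
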